### 2.2. Study Sample

To assess the efficacy of an MTM-based intervention aimed at promoting responsible gambling among college students, participants will be recruited from the student population of a southwestern university. This sampling approach was chosen for its accessibility and the notable prevalence of gambling behaviors within this demographic [16]. Given that the legal gambling age in the United States is typically 21 [17], the eligibility criteria for this study will include the following:Enrollment as a student at the southwestern college.Age 21 or older.Proficiency in English.A score of 3 or higher on the PGSI [14].Consent to participate in this study.

Students currently undergoing treatment for gambling issues will be excluded to prevent potential confounding effects associated with concurrent interventions.

The Problem Gambling Severity Index (PGSI), a standardized tool for assessing gambling-related risk behaviors [14], will be used to screen the participants. Individuals scoring between 3 and 7 on the PGSI are classified as moderate-risk gamblers, indicating behaviors such as exceeding gambling budgets, losing track of time, or experiencing guilt over gambling [14]. A score of 8 or higher designates an individual as a problem gambler, reflecting significant gambling-related issues [14]. Therefore, students scoring 3 or above on the PGSI who meet all other eligibility criteria will be included in this study.

### 2.3. Sample Size Calculation

A power analysis was conducted using G*Power (version 3.1) [18] to estimate the required sample size for this study. Based on a Two-Way Mixed Analysis of Variance (ANOVA) with a medium effect size of 0.30, two intervention groups, three time points (pre-, post-, and follow-up), an alpha level of 0.05, and a beta of 0.20 (80% power), the analysis assumed a correlation of 0.5 among repeated measures and applied a non-sphericity correction of 1. The calculation indicated a required sample size of 20 participants per group. To account for potential attrition and missing data, the sample size was increased by 50%, resulting in a total of 60 participants, with 30 in each group.

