### 2.13. Inferential Statistical Methods

This study utilizes the following inferential statistical methods to evaluate the intervention’s impact as indicated in Table 3:Two-Way Mixed Analysis of Variance (ANOVA): The repeated measures analysis will be used to assess mean differences over time (pre-test, post-test, follow-up) within subjects and between the experimental and comparison groups. This test will be applied to evaluate changes in PGSI scores and MTM construct scores across the three-time points, capturing both within-subject effects (e.g., changes over time) and between-group effects (e.g., differences between the experimental and comparison groups due to the intervention) [23]. This approach allows for a thorough understanding of how the participants’ gambling behaviors and MTM constructs evolve during the course of the intervention, while accounting for the repeated nature of the measurements.Mixed Analysis of Covariance (ANCOVA): If significant baseline differences are identified in key variables (e.g., PGSI scores, MTM construct scores, or demographic factors like age or gender), an ANCOVA will be incorporated into the model to control for these differences. For instance, if the participants in one group have significantly higher baseline PGSI scores, the ANCOVA will adjust for this disparity, ensuring that the observed effects on responsible gambling behavior are attributable to the intervention rather than to pre-existing variations between groups [23]. This statistical approach enhances the precision of the findings by accounting for baseline differences, allowing for a more accurate assessment of the intervention’s impact.

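### The stated 20 participants per group does not follow from the listed G*Power inputs, and the powered effect is not named

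*Protocol article*

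**What the plan says.** Section 2.3 (Sample Size Calculation) describes the calculation as "Based on a Two-Way Mixed Analysis of Variance (ANOVA) with a medium effect size of 0.30, two intervention groups", with "three time points (pre-, post-, and follow-up") and "an alpha level of 0.05". It adds 80% power, a correlation of 0.5 among the repeated measures and a non-sphericity correction of 1, all run in G*Power 3.1. The reported result is: "The calculation indicated a required sample size of 20 participants per group". That makes 40 in total, which is then raised by half for attrition and missing data to 60, or 30 per group.

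Section 2.3 does not say whether the calculation concerns the time effect, the group effect or their interaction. Section 2.13 (Inferential Statistical Methods) says the model will be read for within-subject effects and for "between-group effects (e.g., differences between the experimental and comparison groups due to the intervention"). Table 3 speaks of within- and between-group differences over time.

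**The concern.** A two-way mixed ANOVA contains three testable effects, and G*Power has a separate procedure for each. At the same f and correlation, the within-subject and interaction tests need far fewer participants than the between-group test. A reader given every input except the choice of effect should still find that one of the procedures returns 40 in total. If none does, the only numerical justification of the sample size in the article cannot be checked, and readers cannot tell what 40 completers can detect. Some would overestimate the chance of finding a group difference averaged over visits. Others would read a null interaction as good evidence against a moderate benefit.

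**Working it through.** **Inputs (section 2.3).** f = 0.30, k = 2 groups, m = 3 measurements, alpha = 0.05, target power 0.80, correlation rho = 0.5, epsilon = 1. The metric of the 0.30 is not named. Cohen's f is assumed because it is what G*Power uses for ANOVA. N is the total sample size, and only even totals are considered.

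**The plan's own figure.** 20 per group × 2 = 40, and 40 × 1.5 = 60. The inflation step is consistent with the text. The 40 is what has to be reproduced.

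**Group-by-time interaction, default option.**
- lambda = f² · N · m · epsilon / (1 − rho) = 0.09 × N × 3 / 0.5 = 0.54N
- df = (k − 1)(m − 1) = 2 and (N − k)(m − 1) = 2(N − 2)
- N = 18: power 76.3%. N = 20: 81.2%. N = 40: 98.8%. N = 60: above 99.9%.
- Required: 20 in total, 10 per group. The within-subject (time) effect has the same lambda and the same df here, so it gives the same answer.

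**Between-group main effect.**
- lambda = f² · N · m / (1 + (m − 1) · rho) = 0.09 × N × 3 / 2 = 0.135N
- df = k − 1 = 1 and N − k = N − 2
- N = 40: power 62.0%. N = 60: 79.9%. N = 62: 81.2%.
- Required: 62 in total, 31 per group.

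**Alternative effect-size options for the interaction.**
- Cohen-style: lambda = f² · N · (m − 1) = 0.18N. N = 56 gives 80.7%, so 56 in total. Power at 40 is 65.0%.
- SPSS-style: lambda = f² · (N − k) · (m − 1) = 0.18(N − 2). N = 58 gives 80.8%, so 58 in total. Power at 40 is 62.6%.

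**Summary.**

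| Effect or option | Total N for 80% | Power at 40 | Power at 60 |
|---|---|---|---|
| Interaction or within, default | 20 | 98.8% | >99.9% |
| Between-group | 62 | 62.0% | 79.9% |
| Interaction, Cohen-style option | 56 | 65.0% | 83.6% |
| Interaction, SPSS-style option | 58 | 62.6% | 82.2% |

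The multivariate (MANOVA) approach to the interaction gives 22, and a one-way ANOVA on a single measurement gives 90. A total close to 40 appears only when a stated input is changed. Examples are the interaction with f = 0.20 (42), the interaction with correlation 0 (38), the between-group effect with correlation 0.1 (38) or with f = 0.375 (40), and the interaction at 99% power (42).

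**What f = 0.30 means for the interaction.** Suppose the groups are equal at pre-test and differ by d SD at both later visits. The interaction deviations in each group are then ±(−d/3, d/6, d/6). Their mean square is (d²/9 + d²/36 + d²/36)/3 = d²/18, so f = d/√18. On the default option f = 0.30 therefore means d = 0.30 × 4.243 = 1.27 SD.

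Solving the default interaction test for 80% power gives f = 0.204 at N = 40 and f = 0.166 at N = 60. These correspond to d = 0.87 SD and d = 0.70 SD.

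**The case against.** The best defence is that nothing is short. A sample size for 80% power is a minimum, and group-by-time is the natural test of a randomised pre-test, post-test and follow-up comparison. On the default option, 40 completers exceed the target for that test by a wide margin. This stands, and it limits the point: a reader might infer that the trial is underpowered whichever effect is meant, and the figures do not support that. The shortfall arises only for the between-group main effect or under the alternative options.

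A reader might also infer that section 2.13 commits the trial to the between-group main effect, so that 62.0% is the true power. The wording does not go that far. The phrase "between-group effects (e.g., differences between the experimental and comparison groups due to the intervention") is an example inside a sentence about change across three time points, and Table 3 also refers to differences over time. What can be said is that both kinds of effect will be read and neither is named as the one powered.

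The most likely cause is that G*Power's total of 20 was read as a per-group figure. The article cannot confirm this, and an unreported input would also explain a total near 40.

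The label in "with a medium effect size of 0.30" is not an error in itself. The 1.27 SD translation depends on the default option, the correlation of 0.5 and an assumed sustained difference, and section 2.3 states no response pattern. It is a reason to report the detectable difference, not a separate fault.

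Finally, full retention of 60 would bring the between-group effect to 79.9%. That does not rescue the sentence, because the extra 20 participants are presented as an allowance for attrition and missing data.

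**Conclusion.** The point holds as a reporting error in the sample-size statement. The listed inputs lead to a total of 20, 62, or 56 to 58, depending on effect and option, and not to 40. At 40 completers the power is 98.8%, 62.0%, or 63% to 65%, and the stated 80% matches none of these. The direction of the error depends on an effect that section 2.3 does not name: conservative for group-by-time on the default option, optimistic otherwise.

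The conclusion assumes that 0.30 is Cohen's f and that the standard noncentral-F formulas behind G*Power's repeated-measures procedures apply. The recruitment target of 60 is not shown to be wrong.

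**What to change.** Keep 60 participants and rewrite the paragraph in section 2.3:

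- Name the powered effect. Group-by-time is the natural choice.
- Name the effect-size metric and the G*Power option used.
- Replace the per-group requirement and the 80% with the figures for that effect. For group-by-time on the default option, these are 20 in total for 80% power, with 98.8% at 40 completers.
- State the standardised difference detectable with 80% power at 40 completers and at 60, with the response pattern assumed. For group-by-time with a difference sustained at both later visits, it is about 0.87 SD and 0.70 SD, against the 1.27 SD that f = 0.30 implies on the default option.
- If the original output shows a different input, correct the list of inputs instead.

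The cost is a text correction. No participants, visits or analyses are added. The stated sensitivity becomes less flattering but can be checked.

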### 2.4. Study Procedure

Participant recruitment will target college students aged 21 and older at the university. The recruitment efforts will include email invitations that introduce this study and invite eligible students to participate. The intervention sessions will be conducted in person. The participants will be randomly assigned to either the experimental group (RESPONSIBLEPLAY^©^: MTM-based intervention) or the comparison group (knowledge-based intervention) using SAS PROC SURVEYSELECT. Participant data will first be imported from an Excel file, and each participant will be assigned a unique ID. Simple random sampling (SRS) will then be conducted using PROC SURVEYSELECT, ensuring equal probability of assignment to either group. A fixed seed (12345) will be used to ensure reproducibility. The function will generate a selection indicator (Selected = 1 for the experimental group and Selected = 0 for the comparison group), which will be used to assign the participants accordingly. The final randomized dataset, including group assignments, will then be exported for implementation.

The intervention will be conducted over three weeks, with one session scheduled per week. Each session will span three days, offering multiple time slots to accommodate the participants’ schedules. This approach ensures that all the participants receive the same intervention content while allowing flexibility in attendance. The first session (Week 1) will include an orientation, completion of the pre-intervention survey, and the start of the intervention activities. The final session (Week 3) will consist of intervention activities followed by the post-intervention survey.

To enhance attendance and engagement, the participants will receive email reminders before each session. Additional reminders will be sent to the experimental group between sessions and after the intervention to reinforce the practice of responsible gambling behaviors. At the eight-week follow-up, the participants will attend a final assessment session, which will be scheduled in advance. Email reminders will also be sent to maximize participation.

The intervention content is designed to foster both the initiation and sustenance of responsible gambling behaviors. To support initiation, participatory dialogue will be encouraged through activities such as brainstorming, group discussions, interactive quizzes, and photovoice projects. Behavioral confidence will be enhanced through role-playing scenarios and interactive demonstrations of responsible gambling techniques. The construct of changes in the physical environment will focus on increasing access to resources, including informational brochures, support group contacts, and self-help tools.

To sustain responsible gambling behaviors, three key constructs are emphasized. Emotional transformation is fostered through psychodrama sessions and emotional intelligence workshops. Practice for change is reinforced through social media engagement, journaling, and the use of a responsible gambling app. Changes in the social environment are promoted by building social support networks through peer support groups and mentoring programs.

These strategies are meticulously designed to enhance participant engagement, ensure the standardized delivery of the intervention, and facilitate comprehensive data collection throughout this study. Figure 3 illustrates the MTM framework.

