## 2. Materials and Methods

### 2.1. Study Design

This study will implement a three-week, single-blinded educational randomized controlled trial (RCT), followed by an eight-week follow-up phase (ClinicalTrials.gov number: NCT06642155). The RCT design, widely recognized as the gold standard for evaluating intervention efficacy, was selected for its ability to minimize bias and establish causal relationships between the intervention and its outcomes through randomization [12]. To ensure methodological rigor and transparency, this study will adhere to the CONSORT checklist for RCTs [13], maintaining high standards of reporting throughout the research process. Figure 1 presents the CONSORT flow diagram.

To evaluate changes in health behavior among the participants, this study will administer pre-, post-, and follow-up assessments using the Multi-theory Model (MTM) constructs [10] and the Problem Gambling Severity Index (PGSI) [14]. The participants will be randomly assigned to one of two groups: the experimental group, which will receive the RESPONSIBLEPLAY^©^ MTM-based intervention, or the comparison group, which will receive a knowledge-based intervention. Random assignment, a fundamental component of RCTs, ensures that all the participants have an equal likelihood of being placed in either group. This approach minimizes selection bias, enhances the validity of the findings [15], and helps balance both known and unknown confounders between groups. Consequently, any observed differences in outcomes can be confidently attributed to the intervention rather than to pre-existing disparities [15]. Figure 2 presents an overview of the study design for evaluating the efficacy of responsible gambling interventions.

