This study relies on the PGSI as one of the key outcome measures. While the PGSI is a widely validated and commonly used instrument, its 12-month recall period may limit its sensitivity to detecting short-term behavioral changes resulting from the intervention. To address this, we will supplement our analyses with MTM construct scores, which are specifically designed to measure short-term behavioral initiation and sustenance. Additionally, we will conduct item-level analyses of the PGSI responses (e.g., related to gambling expenditure, time lost, or emotional impact) to assess whether certain dimensions demonstrate greater sensitivity to short-term change. While the PGSI was selected for its classification utility and comparability across studies, we acknowledge that it is best suited for long-term assessments. Accordingly, we are also exploring the feasibility of a 6- to 12-month follow-up study to better align with the PGSI’s recall window and to assess sustained changes in gambling behavior. This extension will depend on participant retention and funding availability but would provide a more complete evaluation of the intervention’s longitudinal impact.

While simple randomization is used for group assignment, we acknowledge that this method may result in imbalances in baseline characteristics, particularly in smaller samples. Although reproducibility was ensured through the use of a fixed seed in SAS, future studies may benefit from using stratified or block randomization to enhance group comparability.

Lastly, the self-reported nature of gambling behaviors, while necessary for understanding personal habits and attitudes, introduces the potential for recall and social-desirability biases. The participants may underreport or overreport their gambling behaviors due to memory lapses or the desire to present themselves in a more socially acceptable light. To address these biases, future studies could incorporate objective measures or third-party reports to provide a more accurate assessment of gambling behaviors and the intervention’s impact.

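### Allocation is an unstratified draw although the screening PGSI band is known beforehand; with 30 per arm a moderate severity imbalance is plausible and cheap to avoid

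*Protocol article*

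**What the plan says.** - **Allocation (section 2.4).** The draw is made on an existing list: "Participant data will first be imported from an Excel file, and each participant will be assigned a unique ID". Then: "Simple random sampling (SRS) will then be conducted using PROC SURVEYSELECT, ensuring equal probability of assignment to either group". A fixed seed is given, and no stratum or block is used.
- **Size (section 2.3).** "the sample size was increased by 50%, resulting in a total of 60 participants, with 30 in each group".
- **Severity (section 2.2).** The PGSI is the screening tool and entry needs a score of at least 3. Scores of 3 to 7 are moderate risk. For the upper band: "A score of 8 or higher designates an individual as a problem gambler, reflecting significant gambling-related issues". There is no upper limit.
- **Limitation (section 3.2).** The authors accept that simple randomisation may leave baseline imbalance in smaller samples and add that "future studies may benefit from using stratified or block randomization to enhance group comparability".
- **Claim from randomisation (section 2.1).** "any observed differences in outcomes can be confidently attributed to the intervention rather than to pre-existing disparities".
- **Analysis (section 2.13).** The default is a two-way mixed ANOVA with the pre-test as one of three time points. ANCOVA is used only if a baseline difference is found to be significant.

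**The concern.** The plan mixes two named severity groups, has the score that separates them before allocation, and allocates from a list in one run. Those are the conditions in which stratification is easiest. The authors name both the weakness and its remedy, then decline the remedy for this trial. Section 2.1 nevertheless speaks of attribution with a confidence that section 3.2 qualifies.

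At stake is the precision and credibility of one small comparison. If one arm happens to hold more severe gamblers, the change in PGSI is partly regression to the mean. The only planned protection switches on after a significance test that has little power at this sample size.

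**Working it through.** **1. Size.** 20 per group × 1.5 = 30 per group, 60 in total, as section 2.3 states. How the 20 was derived does not matter for this point.

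**2. Imbalance in the 8-and-above share.** Let K of the 60 score 8 or more. The documents do not give K, so shares of 10% to 50% are assumed. With 30 drawn from 60, the number X in the experimental arm is hypergeometric (60, K, 30), and the gap between arms is |2X − K|/30. A gap of 20 points means |2X − K| ≥ 6.

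| Assumed share (K) | SD of gap, points | P(≥10 points) | P(≥20 points) | P(≥30 points) | P(≥20 points) if 20 per arm remain |
|---|---|---|---|---|---|
| 10% (6) | 7.8 | 0.20 | 0.02 | 0.00 | 0.11 |
| 20% (12) | 10.4 | 0.33 | 0.10 | 0.002 | 0.24 |
| 30% (18) | 11.9 | 0.40 | 0.16 | 0.01 | 0.30 |
| 40% (24) | 12.8 | 0.43 | 0.19 | 0.02 | 0.33 |
| 50% (30) | 13.0 | 0.44 | 0.20 | 0.02 | 0.34 |

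The last column assumes dropout unrelated to arm or severity. It is relevant because section 2.11 settles on a per-protocol analysis only. Stratifying the draw limits the initial gap to one person, 1/30 = 3.3 points.

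**3. Imbalance in mean PGSI.** In SD units the difference between arms has standard deviation √(2/30) = 0.258. P(|gap| > 0.3) = 2 × [1 − Φ(0.3/0.258)] = 0.245. P(|gap| > 0.5) is about 0.05.

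**4. Would the planned ANCOVA be triggered?** A two-sample t-test on 58 degrees of freedom needs a gap of about 2.00 × 0.258 = 0.52 SD, which occurs with probability about 0.045. So (0.245 − 0.045)/0.245 = 0.82, about four in five, of the gaps above 0.3 SD would stay unadjusted. On the band itself, a 20-point gap gives an uncorrected chi-square p of about 0.05 (3 v 9), 0.09 (6 v 12) and 0.12 (12 v 18). Only at the lowest assumed share (0 v 6) is it clearly significant, p about 0.01.

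**5. Cost under the default analysis.** Take the change from pre-test as the effect contrast, unit SD, and the correlation of 0.5 from section 2.3.

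- A baseline gap of 0.3 SD leaves an expected difference in change of 0.3 × (1 − 0.5) = 0.15 SD with no treatment effect.
- Variance of change: 2 × (1 − 0.5) = 1. Unstratified SE: √(2 × 1/30) = 0.258.
- Stratified, with normal scores and one third in the upper band (assumed): the band means are φ(0.431)/(1/3) = 1.091 and −0.545, so the between-band variance is (1/3)(1.091²) + (2/3)(0.545²) = 0.595. Change has slope −0.5 on baseline, so the band explains 0.25 × 0.595 = 0.149 of its variance. SE: √(2 × 0.851/30) = 0.238.
- Simulations under these assumptions gave about 0.257 unstratified and 0.236 to 0.241 stratified. The reduction in SE is roughly 6% to 8%.
- With baseline PGSI as a covariate in every case: √(2 × (1 − 0.25)/30) = 0.224. Simulation gave 0.226 with or without stratification.

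**The case against.** Simple randomisation is a valid design. It preserves the type I error rate and gives an unbiased estimate, and its standard error already covers chance imbalance. The authors disclose the risk in section 3.2, which qualifies the generic sentence in section 2.1. Once baseline PGSI is in the model, stratification adds nothing measurable. All of this stands. It makes the point one of avoidable imprecision, and it makes unconditional adjustment the more valuable half of the remedy. It does not rescue the plan as written, because section 2.13 adjusts only after a significant baseline test.

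Three practical objections also stand in part:

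- Section 2.4 does not say that the imported file holds the screening PGSI. That it could is an inference from section 2.2.
- The pre-test is completed in the first session, and sections 2.4 and 2.6 place sessions after allocation and separately by group. The screening band may therefore not match the analysed baseline exactly.
- Section 2.5 describes the protocol as underway, and the article does not show whether the draw has been made.

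A reader might infer that a large imbalance is likely, or that stratification would remove it. The figures do not support this. A gap of 20 points has at most about a one in five chance at 30 per arm, a gap of 30 points at most about 2%, and score differences within a band would remain. Nor do the documents state that baseline severity is the strongest predictor of outcome. The argument needs only the plan's own correlation of 0.5.

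**Conclusion.** The point holds as a moderate, cheaply avoidable weakness in a stated design choice. At 30 per arm the chance of a gap of 20 points or more in the upper-band share is about 2% to 20%, and the chance of a mean gap above 0.3 SD is about 25%. About four in five of those mean gaps would miss the ANCOVA trigger. Under the default analysis, stratification would lower the SE of a change-score effect by roughly 6% to 8%. Under unconditional baseline adjustment that gain disappears.

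The result rests on an assumed upper-band share (10% to 50%; one third for the SE), normal scores for the SE, the plan's correlation of 0.5, and a fixed draw of 30 from 60. It is a recommended change; the allocation method is not an error.

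**What to change.** **If the randomisation run has not been made.**

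- In section 2.4, carry the screening PGSI band (3 to 7; 8 or more) on the imported list, sort by it, and run PROC SURVEYSELECT with a STRATA statement, selecting half of each band. If the bands have odd counts, round one up and the other down to keep 30 per arm.
- In section 2.13, include the band with its interaction with time, or baseline PGSI, in the efficacy model whatever the baseline tests show. A main effect of band alone does not sharpen the change over time, so the interaction is needed. If pre-test PGSI is the covariate, treat only post-test and follow-up as outcomes.
- Amend the sentence in section 3.2 to match.

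**If allocation has already taken place.** Make only the unconditional adjustment, and keep the disclosure in section 3.2.

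**Either way.** Soften the attribution sentence in section 2.1 so that it agrees with section 3.2.

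**Cost.** One SAS statement, short edits to the text, and one or a few degrees of freedom; no extra participants or visits. Differences within a band, and imbalance arising from dropout, will remain.

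### The randomisation seed is stated in advance and no locked list is described, so whoever orders the list could predict or steer allocation

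*Protocol article*

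**What the plan says.** Section 2.4 (Study Procedure) gives the allocation steps in order. The list comes first: "Participant data will first be imported from an Excel file, and each participant will be assigned a unique ID". The draw follows: "Simple random sampling (SRS) will then be conducted using PROC SURVEYSELECT, ensuring equal probability of assignment to either group". The seed is named in the future tense: "A fixed seed (12345) will be used to ensure reproducibility". The output is an indicator, "Selected = 1 for the experimental group and Selected = 0 for the comparison group", and the last step is: "The final randomized dataset, including group assignments, will then be exported for implementation".

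Section 2.3 gives the planned size of the list and of the draw: "resulting in a total of 60 participants, with 30 in each group". Section 2.1 says of random assignment: "This approach minimizes selection bias", and goes on to attribute differences in outcome to the intervention on that basis.

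Section 3.2 (Limitations) counts the fixed seed as a strength, for reproducibility, and concedes only that simple randomisation may leave baseline imbalance. It does not mention predictability. The article does not say who prepares or orders the Excel file, who runs the program, or whether the list is frozen before the run.

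**The concern.** Randomisation protects against selection bias only if nobody who can influence membership or order of the list can know what each place on it will receive. Here the seed is declared ahead of the draw, and the planned list size and group size appear in the same article. What remains open is who is on the list and in which order, and both are settled by whoever prepares the Excel file.

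That person could run the same few lines of code in advance and see the arm attached to each row. Rows could then be reordered, or late entries added or removed, with the resulting arm known. Section 2.2 screens students on their PGSI score, so a prognostic value is available when the list is assembled. With 30 per group, each student is one thirtieth of an arm.

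The reason given for the fixed seed is reproducibility. That does not require the seed to be known beforehand: a seed obtained after the list is frozen, and then logged, reproduces the allocation just as well.

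**Working it through.** **Inputs.** Seed 12345, simple random sampling in PROC SURVEYSELECT, and the order import, IDs, draw, export (all Section 2.4). Required size 20 per group, increased by 50% (Section 2.3).

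**Step 1: planned list size.** 2 × 20 × 1.5 = 60 rows, and 20 × 1.5 = 30 selected. This matches the article's 60 and 30. Only the step from 20 per group to 60 was checked for this point.

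**Step 2: what the draw depends on.** An unstratified draw of fixed size n from N rows is a function of four things: the seed, N, n and the row order. No participant characteristic enters. There are C(60, 30) = 118,264,581,564,861,424, or about 1.18 × 10¹⁷, possible sets of 30 rows out of 60. Once the seed, N and n are fixed, only one set of positions can result.

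**Step 3: demonstration.** SAS was not available, so two standard algorithms for fixed-size simple random sampling (Floyd's method and sequential selection) were run in Python with seed 12345, N = 60 and n = 30. Each returned the same 30 positions in 1000 of 1000 reruns. The two algorithms give different positions from each other, and neither set should be read as the SAS result. The point is determinism, not the particular rows.

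**Step 4: if the list is not exactly 60 rows.** With half of the rows selected and the same seed used for both sizes, agreement with the N = 60 positions, averaged over 2000 seeds, was:

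| Rows | Floyd | Sequential |
|---|---|---|
| 56 | 0.836 | 0.975 |
| 58 | 0.893 | 0.982 |
| 62 | 0.894 | 0.982 |
| 64 | 0.824 | 0.976 |

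Unpredictable allocation would give about 0.50. In these stand-ins, a small departure from 60 rows reduces foreknowledge but does not remove it. Someone who holds the final list needs no approximation, because its length is then known.

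**Step 5: the safeguard.** Between import and export, Section 2.4 describes no freezing of membership or order. The remaining degree of freedom therefore stays open while the seed is already known.

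**The case against.** The strongest reply is that this is a single draw made after participants are listed. Nobody is allocated at the moment of enrolment, where foreknowledge most directly distorts recruitment. If the list is complete and its order was set without regard to the seed, knowing the seed gives little opening. That is correct, and it limits the point: the remaining route is a deliberate change of rows or order. It is also why the remedy is a lock.

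A declared seed has a real merit as well. It prevents trying several seeds until the split looks favourable, and rerunning 12345 on an unchanged list only returns the same split. That stands too, and any replacement must keep this protection.

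Timing is uncertain. Section 2.4 uses the future tense, but Section 2.5 describes the study as underway and Section 3.2 speaks of the fixed seed in the past tense. Allocation may already have been done, in which case the procedure cannot be replaced and only reporting remains.

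Several stronger readings are tempting, and the article does not support them:

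- **Allocation is not concealed.** The article is silent on concealment, and a condensed article may leave it to the full protocol. Silence is not a statement that the list is open.
- **The study team builds the list.** Section 2.4 names nobody.
- **The 30 experimental rows are fixed before anyone enrols.** This holds only if the list has the planned 60 rows, 30 are requested, and row order and software are as foreseen. Sixty is a target.
- **Repeated batches would reuse the same positions.** Section 2.4 describes one draw and one final dataset.
- **The type I error is inflated by a stated amount.** Any such figure would have to assume a number of swapped students and a gap in their outcomes, neither of which the article gives. A simple two-sample comparison would also not represent the planned two-way mixed ANOVA (Section 2.13), in which a severity gap that is constant over time adds nothing to the group-by-time term.

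**Conclusion.** The point holds in a limited form. It concerns a stated choice, namely a seed declared before the draw and justified by reproducibility, and not a detail left out of a condensed article. With that seed and the planned 60 rows and 30 selections, the allocation is a known function of row order, and no list lock is described. Allocation is therefore predictable to whoever orders the list and open to steering, and the claim in Section 2.1 about selection bias is weaker than it reads.

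The size is one of exposure, not of estimated bias: full predictability by row when the list size is known, and 82% to 98% average agreement for nearby sizes in the stand-in algorithms. This assumes that the SAS procedure behaves as any seeded fixed-size simple random draw does. The actual SAS positions were not computed, and nothing in the article indicates that steering has occurred or is intended. The change is worth making because it closes a route to selection bias at almost no cost.

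**What to change.** Replace the fixed-seed sentence in Section 2.4 with a rule in this order:

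1. Complete the participant list, sort it by ID, lock it and time-stamp it. Allow no additions, removals or reordering afterwards.
2. Only then take the seed from a source named in advance whose value does not yet exist, for example a stated digit string from a named public draw on a later date.
3. Run PROC SURVEYSELECT once, archive the log with the seed, and release the assignments afterwards.

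Reproducibility is kept because the seed is logged. Protection against choosing among seeds is kept because the source is named beforehand.

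If allocation has already been done, report when the list was locked relative to the run and whether its order was set independently of the seed. Section 3.2 should then mention predictability alongside baseline imbalance.

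The cost is one paragraph of procedure and a few minutes of work, with no extra staff or participants.
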